# The Walking Interventions Through Texting (WalkIT) Trial: Rationale, Design, and Protocol for a Factorial Randomized Controlled Trial of Adaptive Interventions for Overweight and Obese, Inactive Adults

**DOI:** 10.2196/resprot.4856

**Published:** 2015-09-11

**Keywords:** just in time adaptive interventions, Fitbit, exercise, overweight, inactive, text messaging, SMS, percentile schedule of reinforcement, mHealth

## Abstract

**Background:**

Walking is a widely accepted and frequently targeted health promotion approach to increase physical activity (PA). Interventions to increase PA have produced only small improvements. Stronger and more potent behavioral intervention components are needed to increase time spent in PA, improve cardiometabolic risk markers, and optimize health.

**Objective:**

Our aim is to present the rationale and methods from the WalkIT Trial, a 4-month factorial randomized controlled trial (RCT) in inactive, overweight/obese adults. The main purpose of the study was to evaluate whether intensive adaptive components result in greater improvements to adults’ PA compared to the static intervention components.

**Methods:**

Participants enrolled in a 2x2 factorial RCT and were assigned to one of four semi-automated, text message–based walking interventions. Experimental components included adaptive versus static steps/day goals, and immediate versus delayed reinforcement. Principles of percentile shaping and behavioral economics were used to operationalize experimental components. A Fitbit Zip measured the main outcome: participants’ daily physical activity (steps and cadence) over the 4-month duration of the study. Secondary outcomes included self-reported PA, psychosocial outcomes, aerobic fitness, and cardiorespiratory risk factors assessed pre/post in a laboratory setting. Participants were recruited through email listservs and websites affiliated with the university campus, community businesses and local government, social groups, and social media advertising.

**Results:**

This study has completed data collection as of December 2014, but data cleaning and preliminary analyses are still in progress. We expect to complete analysis of the main outcomes in late 2015 to early 2016.

**Conclusions:**

The Walking Interventions through Texting (WalkIT) Trial will further the understanding of theory-based intervention components to increase the PA of men and women who are healthy, insufficiently active and are overweight or obese. WalkIT is one of the first studies focusing on the individual components of combined goal setting and reward structures in a factorial design to increase walking. The trial is expected to produce results useful to future research interventions and perhaps industry initiatives, primarily focused on mHealth, goal setting, and those looking to promote behavior change through performance-based incentives.

**Trial Registration:**

ClinicalTrials.gov NCT02053259; https://clinicaltrials.gov/ct2/show/NCT02053259 (Archived by WebCite at http://www.webcitation.org/6b65xLvmg).

## Introduction

### Overview

Walking is a low-cost, widely accepted physical activity (PA) associated with significant health benefits [1,2]. However, a meta-analysis by Conn et al [3] found that PA interventions showed improvements of only 14.7 minutes/week (about 2 minutes/day), suggesting more potent interventions are needed. Goal setting is a key component of behavioral theories [4,5] and PA interventions [6]. Though step goals are a key modality to increase PA, differing implementation strategies impede definitive conclusions [7]. Also, inconsistencies in reward structures for goal attainment further impair best practices for behavior change. Principles of operant learning and behavioral economics have the potential to concurrently refine goal setting and incentive strategies in the behavioral sciences [8].

### Percentile Shaping: Adaptive Versus Static Goal Setting

Goal setting approaches are often fixed over time, though typically vary from researcher-assigned [9-12] to participant-selected [7,13,14]. If goals include participant input, it is often to set a starting goal from a baseline value [7]. A review of goal setting approaches for weight loss using PA and diet interventions found mixed results, noting the presence of extensive methodological issues and confounders in most studies [15]. Traditionally, fixed or static goals are the same across individuals (eg, walk 10,000 steps or exercise 30 minutes daily), affording the investigator a simple but insensitive threshold to promote behavior change. A major limitation of static goals is the inherent inflexibility to accommodate the myriad influences on day-to-day behavior (eg, illness, major life events, daily, or other cyclical schedules [16]).

Adaptive goals that adjust frequently and uniquely to an individual’s recent performance may be a more realistic approach to developing flexible yet challenging and attainable goals, but the task remains to standardize treatment dose across participants. Recently, intensively adaptive interventions have gained attention [16,17]. Intensively adaptive interventions require intensive (eg, daily) repeated measures of the tailoring variable(s) and target behavior. Concepts from percentile shaping may be one solution to standardize treatment dose [16,18] and through technology can be coupled with intensive repeated measures to produce intensively adaptive interventions [16,17].

Percentile shaping uses a moving window of recent performance (eg, last 9 observations or days) and a rank-order percentile algorithm to produce adaptive goals that can adjust systematically up or down daily, both within and between individuals, and over time. Percentile shaping capitalizes on the natural variation in behavior to produce personalized goals. Percentile shaping also generates inherently specific, measurable goals that can be explicitly rewarded. Only a handful of studies have tested the use of a percentile shaping approach by providing adapting goals to increase physical activity, and none have orthogonally compared goals derived from percentile schedules with immediate versus delayed reinforcement [16,19,20].

### Reinforcement Schedule: Immediate Versus Delayed

Rewarding small changes in behavior over time is important; however, types and dimensions (eg, latency, schedule) of reinforcement for goal attainment vary widely across interventions [15,16,21-23]. Principles of operant psychology [8] and behavioral economics [24] posit a temporal inconsistency in reward structures for healthy versus unhealthy behaviors. Specifically, “less healthy” behaviors tend to deliver an immediate reward (eg, physical comfort for sedentary behavior), with deleterious effects in the future (eg, lowered physical fitness contributing to heart disease). However, “more healthy” behaviors typically require an immediate cost (eg, physical discomfort for intense exercise) and require a sustained effort to experience delayed rewards (eg, improved physical fitness). As the benefits of healthier behaviors are inherently delayed, the immediate benefit of the less healthy response often wins in the economics of behavior. Interventions that attempt to tip the balance of reward in favor of healthy behaviors through immediate rewards are likely to produce more favorable and longer-term behavior change [16,24-26].

### Purpose and Aims

The purpose is to present the rationale and methods from the Walking Intervention Through Texting (WalkIT) trial—a 4-month, 2x2 factorial randomized controlled trial (RCT) for inactive, overweight, and obese adults. We used a semi-automated text message system to deliver adaptive versus static goals and immediate versus delayed reinforcement. The primary aim was to evaluate whether adaptive goals and immediate reinforcement resulted in a greater change in objectively measured PA compared to the static intervention and delayed reinforcement groups. Daily step counts were measured by a Fitbit device over the course of the 4-month study to evaluate the primary aim. We hypothesized that participants in the adaptive goals and immediate reinforcement groups would increase their average steps/day more than participants in the static goals or delayed reinforcement groups. Secondary aims were to evaluate the effectiveness of the adaptive goal and immediate reinforcement interventions to improve psychological measures, aerobic fitness, and cardiometabolic risk factors.

## Methods

### Overview

The WalkIT trial was a 2x2 factorial RCT conducted over 4 months. Following a 10-day baseline phase to assess usual PA levels measured by Fitbit Zip accelerometers, participants underwent simple randomization using a computerized random number generator for assignment into one of four treatment groups. Main effects of the treatment included Goal Type (adaptive vs static goals) and Reinforcement Type (immediate vs delayed reinforcement). In brief, adaptive goals and immediate reinforcement were based on a percentile-shaping algorithm that adjusted each participant’s goal up and down daily based on their previous nine valid observations (usually the last 9 days) of Fitbit-measured steps. Static goals were set to the recommended 10,000 steps per day and did not change over the course of the study. Participants in the immediate reinforcement group received praise feedback and one reward point each time they met a daily goal, whereas those in the delayed reinforcement group received monthly incentives. All participants received a walking intervention with semi-automated text message–based components. Researchers monitored the text message system for non-standard messages from participants (eg, when a participant asked a question, the research staff was notified), and staff responded through the system.

The Arizona State University Institutional Review Board approved the intervention trial and all the procedures used in data collection. The study is registered as a clinical trial (NCT02053259). See Multimedia Appendix 1 for the CONSORT EHEALTH checklist [27].

### Inclusion and Exclusion Criteria

Participants were generally healthy, inactive, 18-60 years old, with a body mass index (BMI) of 25-55 kg/m^2^ (see Table 1 for complete list of inclusion and exclusion criteria). Initially, criteria were 18-45 years and BMI 25-45 kg/m^2^, but these were increased due to interest and to meet recruitment goals. Attempts were made to contact those previously ineligible who met the expanded criteria. The criteria for determining an inactive participant was defined in two ways. First, physical activity level was screened online with the International Physical Activity Questionnaire (IPAQ) short form. We addressed the limitations of using the IPAQ (eg, recall and social desirability bias) as a pre-screening method by inviting those with ≤1300 metabolic equivalents (MET)-min/week to make an appointment for the office visit. Then, in the 10-day baseline phase prior to randomization, we provided participants with a masked Fitbit (to limit participant reactivity) and monitored wear and steps/day remotely. Inactive participants, defined as those who did not accumulate ≥10,000 steps/day on ≥5 days/week, were randomized to one treatment group. Participants were required to have basic computer literacy, daily access to a personal computer for study-related software, a mobile phone with short message service (SMS, or text) capabilities, and be willing to receive up to 3-5 text messages per day. These criteria were imperative to receiving the mobile health (mHealth) related intervention components.

**Table 1 table1:** Inclusion and exclusion criteria for the WalkIT trial.

Participants		Criteria
**All participants**		
	Home residence	Live in Maricopa County, Arizona.
	Age	Between 18-60 years.
	Body Mass Index	Between 25-55 kg/m^2^.
	Inactive	Not meeting or exceeding physical activity (PA) recommendations (ie, ≥10,000 steps/day on ≥5 days/week).
	Health	No contraindicated condition(s) as assessed via Physical Activity Readiness Questionnaire (PARQ+).
	Medication use	No medication(s) use that prohibits a moderate intensity physical activity program or testing.
	Pregnancy status	Not currently pregnant or planning to become pregnant in the next 4 months.
	Staying within study area	Not planning to leave for ≥10 days or live outside of Maricopa County in the next 4 months.
	Concurrent program	Not currently in a physical activity, diet, or weight loss program (eg, Weight Watchers).
	Computer access	Access to personal Windows or Mac machine on a daily basis.
	Internet access	Access to email and the Internet daily.
	Mobile phone access	Has mobile phone with text messaging; willing to send and receive up to 3-5 texts per day.
**For vascular subset measures**		
	Vaso-active medications	No supplements or over-the-counter medications (eg, calcium, non-steroidal anti-inflammatories) at least 4 days prior to visits.
	Female menstrual phase	Within 7 days of onset of menses or >12 months post-menopause at time of visits.

### Recruitment and Setting

Recruitment emails and paper fliers included a brief study overview, notice of compensation for participating, and instructions on how to receive more information and begin the screening process. Local businesses, government agencies, social networking groups, retail outlets, and university departments were contacted to send the email notice and some elected to post physical fliers for their employees or patrons. Focused recruitment of minority populations was conducted through a free online social group advertisement.

Interested participants were directed to a secure online survey system (Qualtrics, LLC) for a pre-screening step, where they found a brief description of the study and completed the eligibility survey. Those determined to be eligible at pre-screening were contacted via phone and email for a telephone follow-up screening. Written (via online survey check box) and verbal informed consent (via the phone) were obtained at the initiation of each screening, respectively. Over the phone, the study was described in detail to participants, who were then offered opportunities to ask questions about participating and asked to clarify responses from their pre-screening responses to further assess eligibility. Qualified individuals were invited to schedule an appointment at the research office to review the study, provide written informed consent, complete baseline measures, and participate in accelerometer training.

Participants were required to reside in Maricopa County, Arizona, and to agree to make two visits to the research office located in Phoenix, Arizona, for pre- and post-intervention measurements. Rolling recruitment occurred February-August 2014 with data collection completed in December 2014. Weather was anticipated to be an influential confounder as the study occurred chiefly in the warmer months and over a monsoon season. Phoenix has a subtropical dry arid desert climate at low latitude (Köppen climate BWh). Wide variation in seasonal temperatures (eg, average high temperatures: July 41.2°C/106.2°F, December 18.9°C/66.0°F), along with monsoons (which include dust storms and flash floods), may drastically limit outdoor activity on very hot or hazardous days.

The 2013 median annual household income in Maricopa County was US $53,596 [28]. Maricopa County’s majority is white, non-Hispanic (58%), with those identifying as Hispanic or Latino (30%), black (8%), and Asian (4%) being the largest racial/ethnic minority groups [28]. Statewide, 93% of households have access to at least one vehicle [28] and since 2/3 of the state population lives in the recruitment area (ie, Maricopa County), this indicates heavy reliance on car travel within our study area.

### Intervention Groups

Figure 1 shows how intervention groups varied by goal type (ie, adaptive vs static goals) and reinforcement type (ie, immediate vs delayed reinforcement) in a 2x2 design. This design allowed all participants to receive a form of the treatment in an effort to reduce attrition and improve compliance over the duration of the study. During the intervention phase, all participants were asked to self-report steps nightly (ie, before midnight) via the study’s interactive text messaging system that acknowledged their report and provided differential feedback based on group status and performance. The factorial design efficiently tested how each component influenced PA without the use of a “no-treatment” control group. All participants were told their ultimate target behavior was 10,000 steps on ≥5 days per week and that daily goals sent via SMS were good for 1 day only.

**Figure 1 figure1:**
[figure not shown]
Illustration of 2x2 factorial design.

### Experimental Components

#### Goal Setting

Participants received a goal by text message each day they self-reported their steps. The static intervention groups received the standard 10,000 steps per day goal, with immediate or delayed reinforcement for goal attainment. Participants assigned to the adaptive goal group received performance-based goals based on an algorithm developed by the research team. This algorithm was adapted from recent developments in basic science around percentile schedules of reinforcement [18,29]. The preceding nine observations (typically last 9 days) of data were used to derive a rank-ordered percentile goal. The percentile algorithm requires (1) continuous and repeated measurements of PA, (2) ranking of a sample of behavior (steps/day) from lowest to highest, and (3) calculation of a new goal based on an *n*th percentile criterion.

To illustrate, if a participant’s step count for the preceding 9 days was 1000, 1500, 2600, 4500, 5000, 5700, 6300, 8000, 11,000, rank-ordered from lowest to highest, using a 60th percentile criteria, then 5700 steps becomes the participant’s next goal. The baseline phase provides data for the first goal and then a 9-day “moving window” adapts in each new day’s step count to calculate the next goal. The newest step count observation replaces the oldest step count observation. The 60th percentile was chosen based on previous PA research by Adams [16,20].

It is important to highlight that prescribed adaptive goals always fall within each participant’s recent abilities due to the moving window of the last 9 days. This is distinct from the static intervention group, which receives the commonly recommended goal of at least 8000-10,000 steps 5 days/week, which may be well beyond their current abilities. Because adaptive goals adjust daily, participants were informed that each new goal is good for only one day. We believe this encourages participants to send in step reports daily unprompted.

#### Praise Messages

Several health behavior theories indicate that it is critical to praise improvements to develop new behavior or strengthen a habit [8,30,31]. The combination of goals and feedback was expected to provide a strong PA-shaping program. Delayed reinforcement participants did not receive contingent praise for achieving goals but did receive incentives on a monthly basis. Participants assigned to the immediate reinforcement groups received contingent differential feedback depending on whether a daily goal was met. Participants who did not meet the goal were provided a simple confirmation that steps were entered correctly and provided their next day’s goal (eg, “Steps Received. Goal for 4/1/14 is 4525 steps”). This approach avoids negative messages that could be discouraging. Each time a participant met a goal, a single message from the pool of praise messages was sent to the participant (eg, “Well done! You’re steps closer to good health. Goal for 4/1/14 is 4525”). Some messages used the participant’s first name for enhanced personalization.

#### Reward Points and Incentives

Participants assigned to the delayed reinforcement groups received progressively increasing incentives each month for participating in the study (month 1=$5; months 2 and 3=$10 each; month 4=$20; total $45). Participants assigned to the immediate reinforcement groups received a point-based incentive each time they met a step goal. They had the opportunity to earn a point once per day (110 points possible) when a goal was met by the end of the day. Points were automatically exchanged for incentives ($5 for every 5 points earned) during the study. Participants self-selected their incentive from a list of retail options (eg, Amazon, iTunes, Target) or a charity (ie, the United Way), and all incentives were sent as electronic gift cards. To prevent habituation or satiation, they were allowed to change their choice at any time. Incentive amounts for delayed reinforcement groups approximate the total amount made available to the immediate reinforcement groups to control for cumulative amount of incentives.

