### Statistical Analysis

#### Power and Sample Size Determination

To estimate the sample size required to test the main aim of changes to steps/day, we conducted a set of simulations using a SAS macro developed by Psioda [50] and effect size estimates derived from findings reported by Adams et al [16]. Across the simulation runs, we varied the number of participants (Ns of 60-96), the magnitude of change from baseline to intervention Phase (1200 vs 1600 steps/day), magnitude of Goal Type (Static vs Adaptive) x Phase interaction effect (800 vs 1200 steps/day between-group difference in the magnitude of the Phase effect; compare to 1130 steps/day difference reported by Adams et al [16]), magnitude of Reinforcement Schedule (Delayed vs Immediate) x Phase interaction (300 vs 500 steps/day between-group difference in the magnitude of the Phase effect), and the Goal x Reinforcement x Phase interaction (150 vs 300 steps/day difference in Phase effect over and above the main effects and 2-way interaction effects). The simulations revealed that under the most conservative sets of assumptions (ie, sets comprising combinations of the smallest effect magnitudes) and an assumed attrition rate of 20%, a total initial sample size of N=100 participants (n=25 per group) would be required to have power of .80 or greater to detect hypothesized interaction effects.

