## Discussion

### Principal Considerations

This study integrates measures of behavior change and physiological outcomes to evaluate intervention strategies and mechanisms that improve health through adoption of walking behaviors over 4 months in an inactive, overweight/obese adult sample. The study examines the effects of two experimental factors: (1) percentile shaping to produce performance-based adaptive goals, versus typical static goals of 10,000 steps/day, and (2) reward structure using principles of behavioral economics (ie, US $1 per daily goal achieved, obtained immediately as goal achievement is reported), versus a delayed incentive. The group with a combination of static goals and delayed reinforcement approximates procedures found in practical settings (eg, a physician offering a PA brochure, recommending 10,000 steps/day, and giving a pedometer to a patient) with the difference being a predetermined monthly reward for continuing with the study—a common approach in many research studies [16,20,51,52].

Our factorial study design allows examination of the independent and joint effects of these components and explores the promise of percentile shaping and small immediate rewards to optimize behavioral interventions. Our work will contribute to the field by testing specific methodologies that link behavior change theory to practical applications. The limited body of research on shaping to improve PA shows complementary results, even with differing methodological approaches [16,19,20]. Further, employing mHealth strategies, such as SMS for treatment delivery and reward mechanisms, and wearable activity monitoring with feedback and wireless upload, enhance the overall treatment and theoretical fidelity [53] while capitalizing on the omnipresence of mobile technology.

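### Payment for staying in the study is tied to the Reinforcement factor, and a model with random intercepts only leaves the contrasts exposed if low walkers in Static + Immediate stop early

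*Protocol article*

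**What the plan says.** Reward Points and Incentives says: "Participants assigned to the delayed reinforcement groups received progressively increasing incentives each month for participating in the study". The amounts are $5 for month 1, $10 each for months 2 and 3, and $20 for month 4, $45 in total. Principal Considerations describes the same payment as "a predetermined monthly reward for continuing with the study". For the other level of the factor, Reward Points and Incentives says: "Participants assigned to the immediate reinforcement groups received a point-based incentive each time they met a step goal". No payment for continuing is described for the immediate arms. Under Praise Messages, for the immediate arms, "Participants who did not meet the goal were provided a simple confirmation that steps were entered correctly" and the next day's goal.

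Intervention Groups presents treatment for every arm as chosen "in an effort to reduce attrition and improve compliance over the duration of the study". Power and Sample Size Determination uses "an assumed attrition rate of 20" percent, with no split by arm.

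Data Analysis lists what all models will account for. The only random effect named is the person-level intercept, alongside autocorrelated residuals. Missing Data anticipates possibly non-ignorable missingness and plans intent-to-treat, full-information maximum likelihood, multiple imputation and sensitivity analyses.

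Two passages blur the payment rule. Goal Setting describes both reinforcement types in the static groups as tied to attaining goals, which conflicts with the two sections on the delayed payment. Recruitment and Setting says recruitment material gave notice of compensation for taking part, without saying what it was or which arms received it.

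**The concern.** Both levels of the Reinforcement factor must keep wearing and syncing the Fitbit and attend the second visit. As described, one level is paid for doing so and the other is paid for step counts. A Static + Immediate participant who rarely reaches 10,000 steps has little financial reason to continue, while the same walker in Static + Delayed is paid each month. If poor responders left Static + Immediate for that reason, the remaining data would make that cell look better than it is. The cell enters every factorial contrast, so the error would spread to all of them. The pre/post laboratory outcomes are also exposed, because someone who misses the second visit has no post value.

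**Working it through.** **1. Payments.** The delayed total reproduces: 5 + 10 + 10 + 20 = $45. An immediate-arm participant can earn 110 points, paid as $5 per 5 points, so earnings are 5 x floor(points/5).

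- Static + Immediate reaching 10,000 steps on k days a week has 110k/7 points: k = 0 gives $0; k = 1, 15.7 points, $15; k = 2, 31.4 points, $30; k = 3, 47.1 points, $45; k = 4 (still eligible), 62.9 points, $60. Break-even is 45/110 = 41% of days, or about 2.9 days a week.
- Adaptive + Immediate: the goal is the 6th of the last 9 ranked days. With stable, exchangeable days the chance of exceeding it is 4/10, whatever the step level. That gives 0.40 x 110 = 44 points, worth about $44 (slightly less in whole $5 exchanges).

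The shortfall is therefore confined to Static + Immediate participants below about 3 days a week at goal.

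**2. Direction.** If the estimated change in Static + Immediate is too high by d, then Reinforcement x Phase shifts by +d/2, Goal x Phase by -d/2, and the three-way difference of differences by -d.

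**3. Size of d.** The document gives no SDs, so these are assumptions: between-person SD 2000, daily residual SD 3000, AR(1) correlation 0.3, SD of true change 1000 or 2000, 10 baseline and 110 intervention days, and no true effects. In every cell 20% stop: at random in three cells, and the lowest 20% of responders in Static + Immediate. Stopping follows either the underlying change or the change recorded so far. Models were fitted by maximum likelihood to 6,000 simulated people per cell, so the figures are close to pure bias. Values of d in steps/day:

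| SD of change | Stop day | Stopping follows | Intercepts only | Plus random Phase | Equal weight per person |
|---|---|---|---|---|---|
| 1000 | 10 | underlying | +159 | +116 | +6 |
| 1000 | 10 | recorded | +83 | +9 | -183 |
| 1000 | 30 | underlying | +62 | +38 | 0 |
| 1000 | 30 | recorded | +36 | 0 | -62 |
| 2000 | 10 | underlying | +283 | +109 | -1 |
| 2000 | 10 | recorded | +216 | -3 | -145 |
| 2000 | 30 | underlying | +125 | +42 | +6 |
| 2000 | 30 | recorded | +97 | +1 | -41 |

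Halving the intercepts-only column gives main-effect shifts of about 18 to 63 (day 30) and 42 to 142 (day 10). Runs at 25 per cell with stopping on underlying change gave 22 to 79 at day 30. At day 10 with SD 2000 they gave about +160 for Reinforcement and -195 for Goal, with a Monte Carlo error of 25-40. A second set of assumptions (baseline SD 1800, daily SD 2500, SD of change 500-2000, true Goal effect 800, lowest walkers by step level stopping) gave Goal estimates of 776 to 695 at day 14, shifts of 24 to 105, and 790 to 764 at day 30, shifts of 10 to 36.

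**4. Low walkers leaving both static cells.** With stopping on underlying change, the Reinforcement shift falls to between -7 and +4. The Goal shift becomes -148 (SD 1000) or -300 (SD 2000) at day 10, and -60 or -113 at day 30.

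**5. Laboratory outcomes.** If the lowest 20% of responders miss the second visit, a completers-only cell mean moves by phi(0.842)/0.8 = 0.35 SD of change.

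**The case against.** A reader might infer that the payment scheme does bias the factorial contrasts. The documents do not support that. No attrition by arm is reported, and the article says analyses were still in progress. The effect needs selective stopping in Static + Immediate that Static + Delayed does not share. Both cells face the same 10,000-step goal, and if low walkers leave both, the Reinforcement contrast is almost unaffected. The Goal shift that remains then comes from goal difficulty, not payment.

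The larger figures also need very early stopping, before any monthly payment is due, and the first is only $5. The payment gap grows later, where the shift is small. An SD of change of 2000 is high: 0.80 power for 800 steps at 40 v 40, two-sided 0.05, implies about 800/[2.80 x sqrt(2/40)] = 1277. These points stand, and they limit the size.

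A reader might also infer that the immediate arms as a whole are unpaid for staying. Adaptive + Immediate earns about $44, and the unspecified compensation under Recruitment and Setting may have been common to all arms.

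Finally, Missing Data already anticipates non-ignorable missingness and proposes no completers-only analysis. Stopping that follows recorded steps is, in principle, handled by likelihood methods. That holds only if the model is right: with random intercepts only, bias remained even in that case, and the random Phase effect removed nearly all of it. Standard maximum likelihood and multiple imputation also assume missingness at random, and no cell-specific analysis is named.

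**Conclusion.** The concern holds as a risk. As described, payment for continuing is attached to the delayed level of the Reinforcement factor, and the gap falls on low walkers in Static + Immediate. If they stop selectively, the listed model would overstate Reinforcement x Phase, understate Goal x Phase and make the three-way term more negative. Plausible main-effect shifts are about 20 to 80 steps/day for stopping at day 30 and 25 to 190 for day 10. The planned effects are 300-500 for Reinforcement, 800-1200 for Goal and 150-300 for the three-way term, so the smaller effects are the more exposed. These sizes rest on assumed SDs, 20% stopping, its timing, and full selectivity in one cell only; a smaller SD of change or selection on step level gives less. It is a cheap improvement to a pending analysis and does not invalidate the trial.

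**What to change.** Data collection ended in December 2014, so only analysis and reporting can change.

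- **Model.** Add a person-level random Phase effect to the model in Data Analysis. In the check this removed nearly all the bias when stopping followed recorded steps, and roughly a quarter to two thirds when it followed underlying response. Simple equal weighting per person is not a safe substitute, because it over-corrects when stopping follows recorded steps (about -145 to -190 in the cell at day 10).
- **Missing data.** Include goals met and early intervention steps, by cell, in the imputation for steps and laboratory outcomes. Add a cell-specific departure from missingness at random (for example, delta adjustment in Static + Immediate) to the sensitivity analyses.
- **Reporting.** Compare last valid Fitbit day, number of valid days and second-visit attendance across the four cells. If they differ, state that the Reinforcement contrast also carries a difference in payment for retention.
- **Text.** Confirm whether the compensation mentioned under Recruitment and Setting was common to all arms, and reconcile Goal Setting with Reward Points and Incentives and Principal Considerations on what the delayed payment was for.

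The cost is some analysis work and slightly wider intervals; Fitbit and text-message data are already logged. Equal payment for supplying data in all arms is a point for future trials only.
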